#### Data analysis

We will compare baseline measurements female age, body mass index, indication for AID, previous assisted reproductive treatments, previous pregnancies, parity, intoxication and referral status.

The analysis of all outcomes is on an intention-to-treat basis. For ongoing pregnancy we will test non-inferiority on basis of the absolute risk difference with the absolute margin of 12%. We will subsequently estimate differences in the primary and secondary outcomes as relative risks with 95% CI. We will also report p values.

We will evaluate association and interaction with our primary outcome of baseline variables in logistic regression analyses. The baseline variables that we plan to include in these analyses are timing, sperm quality and practice variation.

We will construct Kaplan-Meier survival curves for time to ongoing pregnancy.

For continuous variables, we examine the distribution of the observations, and if normally distributed, we summarise them as means with SDs. If they are not normally distributed, medians and IQRs are reported. For dichotomous data, we provide proportions (or percentages). In addition to the baseline and outcome data, we also summarise the recruitment numbers, those lost to follow-up, protocol violations and other relevant data. We will analyse a maximum of six cycles of IUI or ICI performed within a time horizon of eight months after randomisation.

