### Study population

#### Inclusion criteria

We will study women between 18 and 43 years with a regular cycle, be it spontaneously or after ovulation induction and with an indication for AID.

Indications for AID are medical reasons like obstructive and non-obstructive azoospermia, severely impaired semen quality in couples who do not wish to undergo or were not successful with ICSI, severe rhesus iso-immunisation, prevention of vertical transmission of a genetic defect or prevention of transmission of HIV in couples who do not wish to undergo semen washing, In addition, lesbian couples or single women who apply for AID are eligible to participate.

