#### Randomisation

Randomisation is performed by accessing a web-based data system that is used for randomisation in clinical trials and will be performed centrally with the use of a permuted-block-design with randomly selected block sizes that vary between two, four and six. We used a permuted block design to randomly allocate participants to a treatment and aimed to maintain balance across treatment groups. In this way, the clinician who performs the randomisation cannot predict the next randomisation to follow. Patients are randomised individually. Patients are randomly allocated to either six cycles of IUI in the natural cycle or six cycles of ICI in the natural cycle.

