#### Interventions

In the IUI cycles, ovulation detection is performed with Luteinising Hormone (LH) tests or by transvaginal sonography, depending on the local setting. In case of monitoring with urinary LH tests, women test their urine once per day, starting on an individually calculated cycle day based on their basal body temperature chart. Women are inseminated with processed semen the day after the endogenous LH surge has been detected in the urine sample. Serum LH measurements are performed from day 11 of the menstrual cycle onwards and women are inseminated 1 day after the serum LH rise.^9^ In case follicular growth is monitored by transvaginal sonography, timing of insemination can be performed by ovulation triggering or by measuring serum LH levels. In case of ovulation triggering human chorionic gonadotropin (Pregnyl, Organon, Oss, The Netherlands) is administered when the dominant follicle has a diameter of at least 16 mm. Women are inseminated 36 to 40 hours thereafter. The semen may be processed in two ways. One way is to process the semen against a density gradient centrifugation and/or a washing step with culture medium according to local laboratory protocol after thawing of the—unprocessed—cryopreserved semen and the second way is to process the semen against a density gradient centrifugation and/or washing step with culture medium according to local laboratory protocol before freezing of the semen. In the ICI cycles, ovulation detection is in the same way as in the IUI arm and insemination is also timed identical to the IUI arm. Women are inseminated with unprocessed semen once per cycle, and preferably by a cervical cap.^6^ Before starting a new treatment cycle with IUI or ICI, women undergo a pregnancy test (Human gonadotrophin hormone (hCG) measurement in serum or urine). If the woman is not pregnant the next treatment cycle is started according to protocol. In case of a positive pregnancy test, women are monitored by transvaginal sonography. Monitoring will take place at 5 to 9 weeks of amenorrhoea to check whether an intrauterine gestational sac is present, that is, a clinical pregnancy.

Subsequently, monitoring takes place at 11 to 12 weeks amenorrhoea to register the presence of an intrauterine gestational sac with fetal heartbeat, that is, an ongoing pregnancy.

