#### Power calculation

The study is designed as a non-inferiority trial. We assume that six cycles can be completed within a fixed time horizon of 8 months. Assuming a live birth rate of 40% after six cycles of IUI, we need 208 women per arm with an alpha of 0.05, and a beta of 0.80 to demonstrate the non-inferiority of ICI with a margin of 12%.^7^

The margin of 12% are the differences shown in literature between IUI and ICI.^3^

A limitation of our study is that we use a non-inferiority margin of 12%. Most clinicians and patients would feel that 12% is a rather large and clinically relevant difference.

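### As described, the primary non-inferiority test uses neither female age nor clinic, so a modest amount of free precision is forgone

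*Protocol article*

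**What the plan says.** The Data analysis section sets the primary test: "For ongoing pregnancy we will test non-inferiority on basis of the absolute risk difference with the absolute margin of 12" per cent. It names no covariate or stratification factor for this test. Age appears in the same section only in the list of characteristics to be compared at baseline: "We will compare baseline measurements female age, body mass index, indication for AID", followed by others. A separate logistic regression looks at association and interaction with the primary outcome. The variables named for it are timing, sperm quality and practice variation. Age is not among them, and the regression has no stated role in the non-inferiority decision.

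The Randomisation section says that allocation "will be performed centrally with the use of a permuted-block-design with randomly selected block sizes" of two, four or six, and names no stratification factor.

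The trial enrols "women between 18 and 43 years" at six clinics, five Dutch and one Belgian (Study design). Under Interventions, the method of ovulation detection varies "depending on the local setting", and semen processing follows each laboratory's own protocol.

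**The concern.** The trial is decided by whether one confidence bound lies above -12 points, so any avoidable width in that interval bears directly on the conclusion. The age range is wide and clinics differ in monitoring and processing, so age and clinic are natural candidates to explain some of the variation in outcome. Both are known at randomisation. Using them in the primary estimate would narrow the interval without more women or more data. The planned size has little slack: 208 per arm only just meets 80% power at one-sided 5%.

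There is also a smaller matter of prespecification. The trial is not blinded and the plan compares age between arms, but the article does not say what follows if the arms differ. A decision to adjust that is taken after seeing the comparison would be open to challenge.

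**Working it through.** **Inputs from the Power calculation section.** IUI rate: "Assuming a live birth rate of 40% after six cycles of IUI". Aim: to "demonstrate the non-inferiority of ICI with a margin of 12" per cent. Error rate: "with an alpha of 0.05", with sidedness not stated. Power is taken as 80% and the size is 208 per arm. The ICI rate is not stated; I take it as equal to IUI, 40%.

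**Step 1: reproduce the planned size.** With no covariates, n per arm = (z for alpha + z for power)² × 2 × 0.40 × 0.60 / 0.12².
- One-sided 5%: (1.645 + 0.842)² × 0.48 / 0.0144 = 206.1, so 207, against 208 stated.
- One-sided 2.5%: 261.6, so 262, which does not match.

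The design therefore reaches its planned power with an unadjusted test at one-sided 5%.

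**Step 2: precision and power without adjustment.** SE = √(2 × 0.24 / 208) = 0.0480, or 4.80 points. Power = Φ(0.12 / SE − z) with 0.12 / SE = 2.498.
- One-sided 5%: Φ(2.498 − 1.645) = 80.3%.
- One-sided 2.5%: Φ(2.498 − 1.960) = 70.5%.

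**Step 3: effect of adjustment.** If age and clinic explain a share R² of outcome variance, SE becomes about 4.80 × √(1 − R²). The article gives no R², so I show a range.

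| Assumed R² | SE (points) | Power, one-sided 5% | Power, one-sided 2.5% | Equivalent n per arm, 208 / (1 − R²) |
|---|---|---|---|---|
| 0 | 4.80 | 80.3% | 70.5% | 208 |
| 1% | 4.78 | 80.7% | 70.9% | 210 |
| 3% | 4.73 | 81.4% | 71.8% | 214 |
| 5% | 4.68 | 82.1% | 72.7% | 219 |
| 10% | 4.56 | 83.8% | 75.0% | 231 |

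The gain is about 0.4 to 3.5 points of power at one-sided 5% and 0.4 to 4.5 points at one-sided 2.5%, worth about 2 to 23 women per arm.

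**Step 4: simulation check.** 5,000 trials per setting; 208 per arm; six clinics; age centred on 34 with SD 4.5 and limited to 18–43; odds ratio per year of age 0.95, 0.92 or 0.88; clinic SD 0 or 0.3 on the logit scale (all assumed). R² ran from 1.2% to 8.1%.
- Weakest setting: the empirical SE was 4.76 unadjusted and 4.77 adjusted, so no measurable gain.
- Strongest setting: it fell from 4.80 to 4.67, and power at one-sided 5% rose from 80.9% to 83.7%.
- With a true deficit of exactly 12 points, the rate of false non-inferiority claims at nominal 5% was 5.1% to 5.6% unadjusted and 5.0% to 5.6% adjusted.

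**Step 5: is chance age imbalance a further harm?** Assume an age SD of 5 years. The between-arm difference in mean age then has SD 5 × √(2/208) = 0.49 years. If the pregnancy rate falls by 2 points per year of age, a 1-SD imbalance moves the estimate by 0.98 points. As a share of the unadjusted variance this is (0.98 / 4.80)² = 4.2%. The R² for the same age effect is (5 × 0.02)² / 0.24 = 4.2%. The two are one quantity: the imbalance is already inside the standard error. Falls of 1 and 3 points per year give 1.0% and 9.4%, which is why 1% to 10% is a reasonable range to show.

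**The case against.** The strongest reply is that nothing here is wrong. The sentence fixes a scale and a margin, not an estimator; a standardised risk difference would satisfy it as written. Choice of covariates is usual content for an analysis plan, which is not shown. The unadjusted test is valid, matches the sample size and reaches the planned power. The gain is small and rests wholly on assumed effects of age and clinic. Changing the primary estimator late in an open trial that has recruited since June 2014 also needs care.

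Most of this stands, and it limits the point to an improvement. It does not remove it. The article is not silent on covariates: it names those planned and their role, and gives age none beyond the baseline comparison.

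Stronger readings are tempting but not supported:
- A reader might infer that the plan commits to raw proportions. The article never calls the test crude or unadjusted.
- A reader might infer that allocation is unstratified. The article names no factor; the full protocol may. If clinic was in fact a stratification factor, that would be a further reason to include it in the model.
- A reader might infer that chance age imbalance biases the non-inferiority claim. Steps 4 and 5 show that it is the same forgone precision seen from another side, with no material effect on the error rate.

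**Conclusion.** The point holds as forgone precision in the primary test as described. It is not a bias, an error-rate defect or a contradiction. Its size depends on how well age and clinic predict outcome, which the article does not say. Over an assumed R² of 1% to 10%, with equal true rates of 40%, it is worth about 0.4 to 3.5 points of power at one-sided 5% and 0.4 to 4.5 points at one-sided 2.5%. At the bottom of that range it may not be noticeable. The unstated sidedness of alpha matters more (80.3% against 70.5% without adjustment), but that is a separate question. The case for acting is that the improvement is nearly free, not that the present test fails.

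**What to change.** Before outcomes are seen by arm, state in the analysis plan:

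*The primary estimate is the marginal risk difference (ICI minus IUI), standardised from a logistic model with arm, female age (continuous) and clinic. Its confidence interval is robust or bootstrap, and the lower bound is compared with -12 points. The unadjusted risk difference is reported as a sensitivity analysis.*

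Standardisation keeps the estimate on the marginal absolute scale, so the 12-point margin and the estimand do not change. It also settles in advance how age is handled, whatever the baseline comparison shows.

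The cost is a short piece of analysis text, with no new data and no more women. The price is reliance on a working model. At a 40% rate, 416 women give about 166 events (0.40 × 416) for seven coefficients besides the intercept (arm, age, five clinic indicators), so the model is not heavily loaded. Because the trial is open and an interim analysis is planned at 200 women, the change should be dated and should record who had seen outcomes by arm at that time.

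### Timing and sperm quality enter the logistic models as baseline variables, but realised timing and inseminated-sample quality arise after randomisation, and the latter can differ by arm

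*Protocol article*

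**What the plan says.** The Data analysis section of the protocol article announces a set of secondary models: "We will evaluate association and interaction with our primary outcome of baseline variables in logistic regression analyses". It then names the covariates: "The baseline variables that we plan to include in these analyses are timing, sperm quality and practice variation". The same section opens with a different list, intended for comparing the groups: "We will compare baseline measurements female age, body mass index, indication for AID, previous assisted reproductive treatments, previous pregnancies, parity, intoxication and referral status". None of the variables in that opening list is named for the logistic models.

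The Interventions section says how timing and semen are handled. For urinary LH monitoring in the IUI arm: "Women are inseminated with processed semen the day after the endogenous LH surge has been detected in the urine sample". In the ICI arm: "Women are inseminated with unprocessed semen once per cycle". On timing in the ICI arm: "ovulation detection is in the same way as in the IUI arm and insemination is also timed identical to the IUI arm". The monitoring method varies by clinic: "ovulation detection is performed with Luteinising Hormone (LH) tests or by transvaginal sonography, depending on the local setting". On IUI preparation: "The semen may be processed in two ways", that is, after thawing or before freezing.

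The primary analysis is a separate intention-to-treat comparison of the absolute risk difference with the 12% margin. No covariates are mentioned for it.

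**The concern.** A covariate in a treatment-by-covariate model should be fixed before allocation and have one value per woman. Two of the three named variables need not meet either condition. Realised timing is set cycle by cycle. Sperm quality, if taken from the sample actually inseminated, has passed through a preparation step that only one arm receives.

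The planned association and interaction results are what is at stake. Conditioning on inseminated-sample quality conditions on part of the treatment, so a real difference between IUI and ICI could appear to be explained away. An interaction with such a variable could also be read as telling clinicians which women do well with ICI, when it describes something produced by the allocated treatment. Meanwhile the variables that are truly baseline, including age in a population of 18 to 43 years, are not named for these models.

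**Working it through.** **1. Each named covariate against the Interventions section**

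- *Timing.* Insemination follows the LH rise or ovulation triggering in each cycle, up to six times per woman and after randomisation. Realised timing is not baseline. The rule is the same in both arms, so it does not differ by arm by design. Only the clinic's monitoring method could be known beforehand.
- *Sperm quality.* The measurement point is not given. On the inseminated sample it is post-allocation and arm-dependent (processed against unprocessed). As the donor's pre-processing value, arm-specific processing does not alter it. Because IUI semen may be processed before freezing, even a post-thaw value can differ by arm.
- *Practice variation.* As centre or local monitoring method, this is a legitimate pre-randomisation variable.

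**2. Several values per woman**

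The outcome is one value per woman. The Follow up section has women treated until ongoing pregnancy, so the number of cycles depends on the outcome. An early conceiver contributes one or two values and a non-conceiver up to six. A best, worst or total score over cycles would then relate to the outcome through the cycle count alone, and a mean would rest on fewer cycles in those who succeed. This holds even where the arms do not differ.

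**3. Illustration of adjusting for inseminated-sample quality**

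Assumptions, none from the documents: donor quality q is standard normal. Inseminated quality is s = q - g × (ICI), with g the shift between arms in SD. Logit of success = -0.4 + 0.3s, which gives 1/(1 + e^0.4) = 0.401 at s = 0, close to the plan's 40%. The whole arm effect runs through s. Simulation used 400,000 women per scenario.

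| Shift g | True risk difference, ICI - IUI | Arm OR adjusted for s | Arm OR adjusted for donor q |
|---|---|---|---|
| 0 | 0.0 points | 1.001 | 1.001 |
| 0.5 | -3.6 points | 0.995 | 0.857 |
| 1 | -6.8 points | 0.999 | 0.743 |
| 2 | -13.1 points | 1.006 | 0.547 |

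The last column agrees with exp(-0.3g) = 0.861, 0.741 and 0.549 for the three non-zero shifts. Adjusting for s removes the effect, and adjusting for the donor value keeps it. With no shift, neither adjustment does harm.

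**4. Precision available from true baseline variables**

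The plan's own figure first. With 40% in both arms and margin 0.12, n = 0.48 × (1.645 + 0.842)² / 0.0144 = 206.1, so 207 per arm against 208 stated. This matches only with one-sided alpha 0.05; the Power calculation section does not state sidedness, and one-sided 0.025 gives 262.

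Approximate power at 208 per arm = Φ(0.12 / √(0.48(1 - R²)/208) - 1.645), where R² is the share of outcome variance explained by the baseline variables (an assumption):

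- R² = 0: 0.12/0.04804 = 2.498; Φ(0.853) = 0.803
- R² = 0.05: 0.12/0.04682 = 2.563; Φ(0.918) = 0.821
- R² = 0.08: 0.12/0.04608 = 2.604; Φ(0.959) = 0.831

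**The case against.** There are four fair objections, and much of each stands.

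First, a reader might infer that timing differs between the arms by design. The documents say the opposite: ICI detection and timing follow the IUI arm. The timing problem is only that realised timing is per-cycle and post-randomisation.

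Second, sperm quality may mean the donor's pre-processing value, in which case the bias through processing does not arise. This is right, and it makes that part of the point conditional. A condensed article may leave the definition to the full protocol or the SAP. What the article does state, however, is a closed list under a label that fits only some readings of it.

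Third, a reader might infer that the trial's treatment effect would be biased or even reversed. The documents do not support this. The non-inferiority test is on the risk difference with no covariates mentioned, and the logistic models are described as examining association and interaction, without promising an adjusted treatment effect. Nothing supports a reversal.

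Fourth, leaving age out does not bias a randomised comparison, and an unadjusted risk difference is valid. That is so; standardisation is a gain in precision and not the repair of an error. The article also does not say that the opening list serves solely for the group comparison; it simply does not name those variables for the models.

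**Conclusion.** The point holds in a limited form. Timing as realised, and sperm quality if measured on the inseminated sample, are not baseline variables. A logistic model with arm and inseminated-sample quality would adjust away whatever part of the treatment effect acts through that quality. Interactions with either variable would not be baseline subgroup effects. Both can take several values per woman over an outcome-dependent number of cycles.

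The size of any distortion cannot be taken from the protocol. The illustration shows complete removal of the effect, but only because the whole effect was assumed to run through sample quality. The conclusion of the primary non-inferiority test is not affected. The precision gain of roughly 2 to 3 percentage points of power depends on the assumed R² of 5-8% and on one-sided alpha 0.05. The change is worth making because it protects the secondary models from misreading.

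**What to change.** Revise the covariate list in the Data analysis section (or the SAP) before the outcome data are analysed:

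- For the treatment-by-covariate models, use pre-randomisation variables already collected: the woman's age, parity or previous pregnancy, and the reason for donor insemination. Represent practice variation by centre or local monitoring method.
- Admit sperm quality only as the donor's pre-processing value, and state the measurement point.
- Keep realised timing and inseminated-sample quality for an explicitly exploratory per-cycle analysis within arm.
- For precision, estimate the risk difference against the 12% margin standardised for age and the other baseline variables, with the crude difference as sensitivity analysis.

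The cost is wording and a modest amount of analysis work. The woman-level variables are already on the plan's baseline list and centre is known. No further recruitment is needed.

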### Data safety monitoring board

A data safety monitoring board (DSMB) is installed for this trial. In the DSMB, professionals from the fields of fertility and epidemiology are represented. All members have independent positions from the trial study group. An interim-analysis is performed on the primary endpoint when 200 patients have been randomised and all have completed at least 3 months of follow-up to enable retrieval of the outcome ongoing pregnancy. The interim-analysis will be performed by an independent statistician, blinded for the treatment allocation. The statistician will report to the independent DSMB. The DSMB will decide on the continuation of the trial. There are no safety issues liaised to this trial and futility is welcomed as an outcome. The only reason for prematurely stopping the trial is a large difference in ongoing pregnancies. We suggest the Peto approach to be used: if an interim analysis shows a probability of less than 0.001 that the treatments are different in terms of ongoing pregnancy, then the trial should be stopped early.

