#### Primary outcome measure

The primary outcome is ongoing pregnancy leading to live birth. Ongoing pregnancy is defined as a positive heartbeat at 12 weeks of gestation. Only ongoing pregnancies that occur within the first eight months after randomisation count for assessment of the primary endpoint.

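### The interim analysis is placed on the primary endpoint after a three-month minimum too short for that endpoint, and its only stopping criterion is worded in reverse

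*Protocol article*

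**What the plan says.** Everything here comes from the protocol article.

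The section Data safety monitoring board fixes the timing: "An interim-analysis is performed on the primary endpoint when 200 patients have been randomised and all have completed at least 3 months of follow-up". The reason it gives is that ongoing pregnancy can then be retrieved. It next limits the grounds for stopping: "The only reason for prematurely stopping the trial is a large difference in ongoing pregnancies". It then suggests the Peto approach, under which the trial should end early "if an interim analysis shows a probability of less than 0.001 that the treatments are different in terms of ongoing pregnancy".

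The section Primary outcome measure makes the primary outcome an ongoing pregnancy that ends in live birth. It adds: "Ongoing pregnancy is defined as a positive heartbeat at 12 weeks of gestation". Only ongoing pregnancies arising in the first eight months after randomisation count; the abstract dates this by conception. The section Power calculation assumes that six cycles fit into those eight months.

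**The concern.** There are two faults in one short section.

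First, the look is said to be on the primary endpoint, but the guaranteed follow-up is three months, while the endpoint needs eight months of treatment and then a birth. For the most recently randomised women, neither success nor failure on that endpoint can be settled. The board would see a mixture of exposure lengths under a label that does not describe it.

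Second, the sentence that triggers stopping asks for a very small probability that the treatments differ. Read literally, that stops the trial when a difference is almost ruled out, the reverse of the sentence before it. This is the trial's only stopping criterion. In a non-inferiority trial, stopping because the arms look alike is a misreading that someone could plausibly make.

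**Working it through.** **1. The plan's own figure.** The section Power calculation gives: "The study is designed as a non-inferiority trial"; "Assuming a live birth rate of 40% after six cycles of IUI"; "we need 208 women per arm with an alpha of 0.05"; "a beta of 0.80 to demonstrate the non-inferiority of ICI with a margin of 12" (per cent). I read 0.80 as power, and assume equal true rates and a one-sided alpha, since sidedness is not stated.

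n per arm = (1.645 + 0.842)² × (0.4×0.6 + 0.4×0.6) / 0.12² = 6.183 × 0.48 / 0.0144 = 206.1, so 207 against 208 stated. The figure is reproduced (one-sided 0.025 would give 262). The interim analysis plays no part in it.

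**2. What a woman at the three-month floor can show.** Three months = 3 × 365.25/12/7 = 13.04 weeks. With gestation counted from about two weeks before insemination, 12 weeks of gestation falls 10 weeks after insemination. The latest useful insemination is 13.04 − 10 = 3.04 weeks after randomisation, about day 21. The section Interventions allows the scan at 11 to 12 weeks; an 11-week scan gives 13.04 − 9 = 4.04 weeks, about day 28. Either way this is roughly cycle 1.

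**3. What share of pregnancies that is.** A constant per-cycle rate giving 40% over six cycles is 1 − 0.6^(1/6) = 8.2%. One cycle then yields 0.0816/0.40 = 20% of her expected pregnancies.

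**4. Live birth.** A term birth at 37 to 40 weeks comes 35 to 38 weeks after insemination, at least 8.0 to 8.7 months after randomisation. It cannot be seen at three months.

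**5. How many of the 200 could be incomplete.** The section Study design gives recruitment from 3 June 2014 to an expected 1 January 2020, which is 66.96 months. Uniform accrual (my assumption) is 416/66.96 = 6.21 per month. If a status needs T months and the last woman has 3, those short of T number at most (T − 3) × rate, capped at 200:

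- Eight months, if the pregnancy itself must fall in the window: (8 − 3) × 6.21 = 31.
- Eight months plus 10 weeks, if conception must: (10.30 − 3) × 6.21 = 45.
- Eight months plus 38 weeks, for live birth: (16.74 − 3) × 6.21 = 85.

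These are upper limits, because some of these women will already have a settled result. Under other assumed rates:

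| Women per month | Short of 8 months | Short of 8 months + 10 weeks | Short of 8 months + 38 weeks |
|---|---|---|---|
| 6.2 | 31 | 45 | 85 |
| 10 | 50 | 73 | 137 |
| 15 | 75 | 109 | 200 |
| 30 | 150 | 200 | 200 |

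**6. When the look would have fallen.** 200/6.21 = 32.2 months after 3 June 2014, so the 200th woman enters in early 2017 and the look follows three months later. The article appeared in July 2019.

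**7. The two stopping sentences side by side.** One permits stopping only for a large difference. The other stops when the probability of a difference is below 0.001. A large observed difference makes that probability high, not low, so the two cannot be met together. The conventional rule that seems intended is two-sided p < 0.001, that is |z| > 3.29. With 100 women per arm, 40 against 18 pregnancies would cross it: z = 0.22 / √(0.29 × 0.71 × 2/100) = 3.43.

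**The case against.** The strongest reply has four parts.

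- **Three months is a minimum.** At the article's average accrual, about 155 of 200 women (77%) would have complete ongoing-pregnancy status, or about 169 (84%) if the pregnancy itself must fall within eight months. A reader might infer that the board would see only first-cycle results. The text does not support that: it holds only for women near the floor.
- **The section names ongoing pregnancy as what is retrieved and compared.** Live birth may never have been meant for the interim, which weakens the figure of 85. This stands, and it is why the label primary endpoint is the error.
- **No false stop is shown.** A reader might infer that unfinished women are counted as failures. The article does not say so, and the interim test may be set out elsewhere. Even if they were, timing is the same in both arms, and fewer events make p < 0.001 harder to reach. With 100 per arm, the chance of crossing at 40% against 28% is 6.5%; on first-cycle rates alone (8.2% against 5.3%) it is 0.6%. Futility is not a ground for stopping.
- **The reversed sentence can be read correctly from its surroundings.** A reader might infer a plan to stop for similarity. The preceding sentence and the reference to the Peto approach rule that out. The rule is also only suggested, and the board decides.

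These points lower the severity. They do not remove the mismatch between the named endpoint and the guaranteed follow-up, nor the contradiction between adjacent sentences. Reading follow-up as starting when treatment ends would suit ongoing pregnancy, but the text does not say this, and live birth would still be unknown.

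**Conclusion.** Wrong as written, of moderate severity. An analysis on the primary endpoint does not fit a three-month minimum when that endpoint spans eight months and requires live birth. Up to about 31 to 45 of 200 women would lack complete ongoing-pregnancy status and up to about 85 live-birth status. The counts rest on uniform accrual of 6.2 per month; slower accrual before the look would shrink them and faster accrual would raise them. The range 31 to 45 reflects the two ways in which the article dates the eight-month window.

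The stopping sentence is inverted. Its intent is recoverable, but it is the sole criterion and should say what is meant. No effect on the sample size or the final analysis is shown.

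**What to change.** - **Outcome.** Call the interim outcome ongoing pregnancy, not the primary endpoint, and state the data cut.
- **Analysis.** Compare time to conception of an ongoing pregnancy by log-rank, censoring each woman about 10 weeks before the data cut. This needs no delay, since every woman still contributes at least about 3 weeks, and it agrees with the Kaplan-Meier curves planned under Data analysis. Alternatively, compare proportions only among women randomised at least eight months plus 10 weeks before the cut. Selecting by randomisation date avoids admitting early pregnancies while leaving out pending women. The price is fewer women (about 155 at the planned date under the accrual above) or a look about 10.3 − 3 = 7.3 months later.
- **Rule.** Restate it as: consider stopping if the two-sided p-value for the hypothesis of no difference in ongoing pregnancy is below 0.001.
- **If the look has already been done**, which the dates make likely, moving it is moot. Report the outcome, data cut and rule actually used.

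The cost is wording in the protocol and in any charter for the board. The 208 per arm stays as it is.
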